### Recruitment of participants

Workers without a permanent employment contract who have applied for a sickness benefit at the Dutch SSA and are sick-listed between one and two weeks, will receive an invitation package from the medical advisor of the SSA, on behalf of the researchers. It contains an invitational letter, a flyer with more details about the study, a consent form and a short questionnaire with a return envelope. A weekly query of the SSA database will be used for the recruitment of eligible workers.

The short screening questionnaire consists of six questions. The sick-listed worker will be asked to fill in whether he or she is interested to participate in the study and to indicate the day he or she applied for a sickness benefit. The Distress Screener, developed by van Oostrom and colleagues [30], will be used as a quick scan for early identification of distress, i.e. three questions of the Four-Dimensional Symptom Questionnaire (4DSQ) will be used to assess the degree of perceived mental health problems. Finally, the sick-listed worker will be asked whether he or she has ‘certainly not/probably not/maybe/probably/certainly’ the intention to RTW if health complaints are still experienced.

In case the sick-listed worker wants to participate and meets the eligibility criteria, he or she will be contacted by the researcher or research assistant for a first intake by telephone. During this intake more information about the study will be given. When the sick-listed worker has indicated to ‘maybe/probably/certainly’ have the intention to RTW despite health complaints, the sick-listed worker will be invited to participate in the RCT. Using the described exclusion criteria, the researcher or research assistant will decide whether the sick-listed worker is able to participate.

In case the sick-listed worker is able to participate, an intake appointment will be planned at the nearest participating front office of the SSA. During the intake, randomisation will be performed after signing informed consent and fulfilling the baseline questionnaire by the participant.

In Figure 1 the consecutive steps in the study design are summarized.

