### Process evaluation

Based on the framework of Steckler and Linnan a process evaluation will be conducted [45]. The aim of the process evaluation is to determine the compliance with the intervention protocol, the feasibility of the participatory supportive RTW program and to assess satisfaction with the OHC guidance in accordance to this program. Three months after the participant has been assigned to the intervention group, the participant, the OHC professionals of the intervention team and the case manager of the rehabilitation agency will all receive a questionnaire. The OHC professionals and the case manager of the rehabilitation agency will be asked whether the intervention was applied according to the protocol. Additionally, they will be asked about applicability, compliance, satisfaction and barriers regarding implementation of the participatory supportive RTW program. Also the participants will be asked about their satisfaction with the participatory supportive RTW program. These questions are based on the Patients Satisfaction with Occupational Health Services Questionnaire (PSOHSQ) [46] and will be included in the three months questionnaire.

During the participatory supportive RTW program, standardized schemes will be used by the OHC professionals to describe identified barriers for RTW, the formulated solutions, the resulting consensus-based action plan for RTW and a final report. These schemes will be used to collect additional data about the implementation of the participatory supportive RTW program.

An overview of the measures and measurement instruments, including a time path for all measurements, is presented in Table 1.

**Table 1 T1:** Overview of measurements and time path

**Measurement**			** Time path**		
	**Baseline (T0)**	**3 months (T1)**	**6 months (T2)**	**9 months (T3)**	**12 months (T4)**
*Prognostic measures:*					
Demographic characteristics (e.g. age, gender)	X				
Last work (shifts, hours)	X				
Type of worker before reporting sick	X				
Reason reporting sick	X	X			
Interference of complaints (WRQ)	X				
RTW expectations	X	X	X	X	X
RTW interventions	X	X	X	X	X
Satisfaction with OHC	X	X	X	X	X
Health care interventions	X	X	X	X	X
*Primary outcome measure:*					
Duration until first sustainable RTW	X	X	X	X	X
*Secondary outcome measures:*					
Duration of sickness benefit	X	X	X	X	X
Work status	X	X	X	X	X
Severity of mental disorder symptoms (4SDQ)	X		X		X
Perceived general health status (SF-36)	X		X		X

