Quality of life (Euroqol)	X		X		X
ASE determinants (ASE questionnaire)	X		X		X
Work limitations (WLQ)			X		X
Health care utilization (Tic-P)	X	X	X	X	X
Patient satisfaction* (PSOHSQ)		X			

*Patient satisfaction with occupational health care services is only measured in the intervention group (as part of the process evaluation).

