### Sample size

Time to first sustainable RTW in a competitive job is the primary outcome measure for the power calculation. Based on a recent study on a participatory RTW intervention for temporary agency workers and unemployed workers with musculoskeletal disorders [22] a Hazard Ratio (HR) of 2.0 is assumed to be the minimal clinical and societal relevant ratio. This indicates that the participants in the intervention group RTW twice as quickly compared to the participants in the control group. Furthermore, it is assumed that a minimum of 2/3 of the participants will achieve first sustainable RTW during the first twelve months of the follow-up period [22]. Based on a power of (1-β=) 0.80 and a two-sided significance level of 0.05 (α) a sample size of 100 participants (n = 2 x 50) is needed. Next, potential clustering of cases guided by the same team of OHC professionals is taken into account. To correct for potential clustering of cases an ICC of 0.05 is used and the minimal number of teams is assessed: eight teams of OHC professionals who are trained in guidance according to the participatory supportive RTW program and eight teams of OHC professionals who deliver only usual OHC. Furthermore, based on comparable research [47], a loss to follow-up of 20% is expected. This results in a requisite number of 172 participants (n = 2 x 86).

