### Statistical analysis

After randomisation, participants will remain in the group (intervention group or control group) they are allocated to, according to the intention-to-treat-principle. Descriptive statistics will be used to check for dissimilarities of prognostic factors in the two groups at baseline. If necessary, analysis will be adjusted. A comparison of intention-to-treat-analysis to per-protocol analysis will be used to determine whether protocol deviations might have caused bias. All statistical analysis will be performed at participant level.

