#### Effect evaluation

The duration until first sustainable RTW in a competitive job in both groups will be described by using the Kaplan-Meier method. The Cox proportional hazard model will be used to estimate differences in RTW between the intervention group and the control group, expressed in hazard ratios (HR) for sustainable RTW and the corresponding 95% confidence intervals. Differences between both groups in total number of days at work and total days of sickness benefit during follow-up will be analysed with a general linear model. Differences in other secondary outcome measures will be analysed with the use of longitudinal random coefficient analysis. Clustering of participants within the OHC teams will be taken into account.

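### The only stated adjustment rule depends on observed baseline imbalance, so the 4DSQ, SF-36, Euroqol and ASE analyses are not committed to using their own baseline scores and may lose precision

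*Protocol article*

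**What the plan says.** Two places in the protocol article govern this point.

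- **Statistical analysis, opening paragraph.** "Descriptive statistics will be used to check for dissimilarities of prognostic factors in the two groups at baseline". The next sentence is "If necessary, analysis will be adjusted". No other rule on covariates is given.
- **Statistical analysis, Effect evaluation.** Days at work and days of sickness benefit go to a general linear model. For the rest, "Differences in other secondary outcome measures will be analysed with the use of longitudinal random coefficient analysis", and "Clustering of participants within the OHC teams will be taken into account". Covariates, the coding of time and the contrast to be reported are not given.

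Table 1 sets the measurement times. The rows "Severity of mental disorder symptoms (4SDQ") and "ASE determinants (ASE questionnaire"), and those for the SF-36 and Euroqol, are marked at baseline, 6 and 12 months. All four are listed as secondary outcome measures. Demographics, last work, type of worker and the WRQ are among the items in a separate block of prognostic measures. The WLQ has no baseline mark.

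Recruitment of participants fixes the order of events: "randomisation will be performed after signing informed consent and fulfilling the baseline questionnaire by the participant". Each baseline score is therefore a genuine pre-randomisation measurement.

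**The concern.** A baseline score of the same instrument is usually the strongest single predictor of the follow-up score. Adjusting for it reduces the residual variance in every sample, balanced or not. A rule that lets covariates in only after a look at imbalance uses the wrong trigger.

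As the article is worded, the rule may not reach these scores at all. It speaks of prognostic factors, and Table 1 files the four instruments under outcomes. On a broader reading, a baseline score would enter only where the arms look unequal. Either way the form of the analysis is settled after the baseline data have been seen.

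At stake is the precision of the comparisons on symptoms, general health, quality of life and the ASE determinants, in a trial sized for a time-to-event endpoint.

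**Working it through.** **Inputs from the article.** Waves at 0, 6 and 12 months (Table 1). Planned size 2 x 86 with 20% loss to follow-up (Sample size), which leaves 86 x 0.8 = 68.8, about 69 per arm. The article gives no precision or power figure for these outcomes, so there is none to reproduce.

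**Assumptions.** The article gives no SD and no correlation. Take a common SD s at each wave and the same correlation r between any two waves, with r from 0.4 to 0.6. Clustering within teams is ignored in the arithmetic.

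**Step 1: like-for-like comparison at one wave.** Variance per participant:

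- unadjusted change from baseline: 2(1 - r) s²
- baseline-adjusted score: (1 - r²) s²
- ratio: 2(1 - r) / [(1 - r)(1 + r)] = 2/(1 + r)

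| r | Change | Adjusted | Ratio |
|---|---|---|---|
| 0.4 | 1.20 | 0.84 | 1.43 |
| 0.5 | 1.00 | 0.75 | 1.33 |
| 0.6 | 0.80 | 0.64 | 1.25 |

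The change row is what an arm-by-wave model estimates when baseline is an outcome row, wave is a category and the baseline means are left free.

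**Step 2: the same in standard errors, r = 0.5, 69 per arm.**

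- Change: √(2 x 1.00/69) = 0.170 SD
- Adjusted: √(2 x 0.75/69) = 0.147 SD

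For an illustrative difference of 0.4 SD at one wave (an assumption), power at two-sided 0.05 is 0.65 against 0.77.

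**Step 3: what depends on a model the article does not name.**

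- *Arm by linear time.* Least-squares slope weights at 0, 6 and 12 months are proportional to (-1, 0, +1). With complete data the 6-month score drops out of the slope, and an effect present at 6 months and gone at 12 is estimated as nil.
- *One arm effect pooled over all three waves.* With equal weights, a sustained effect d is estimated as (0 + d + d)/3 = 2d/3.
- *Arm by categorical wave, free baseline means.* The 6-month effect is estimated in full. The only loss is the ratio in step 1.
- *Baseline as covariate, or baseline means constrained equal.* No loss.

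All four are compatible with the sentence in Effect evaluation.

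**The case against.** The strongest objection is that the article specifies no faulty model. A longitudinal random coefficient analysis may carry the baseline score as covariate. The article condenses a fuller protocol or analysis plan that is not shown, and time coding, contrasts and covariates of a secondary mixed model are commonly settled there. This stands. A reader might infer from the method's name that the 6-month effect is discarded or diluted, but the text does not support that, because only the first two models in step 3 behave that way. Even under linear time, the zero weight holds only for complete data. The article expects 20% loss, and in a likelihood-based fit the 6-month scores of participants who miss month 12 still contribute.

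A larger penalty is also tempting. At r = 0.5 the baseline-adjusted mean of 6 and 12 months has variance (1 + r)/2 - r² = 0.50 s², against 1.00 s² for the slope contrast, a ratio of 2.0. But that sets an average over two waves against a 12-month change, which are different estimands, and it reads as a power ratio only if the effect is sustained. If the effect is d/2 at 6 months and d at 12, the adjusted mean estimates 0.75d, and the advantage falls to 0.75²/0.50 = 1.125.

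The objection does not remove the adjustment rule itself. That rule is stated text, it is conditional on observed imbalance, and no exception is made for the baseline scores of the outcomes.

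**Conclusion.** The point holds in a limited form. The article's only stated route to adjustment runs through a check for dissimilar prognostic factors, and it makes no commitment to the baseline score for the four instruments measured at 0, 6 and 12 months. If that leads to an unadjusted change from baseline, its variance at a given wave is 1.25 to 1.43 times that of the adjusted score for r = 0.4 to 0.6, and 1.33 at r = 0.5. These figures rest on assumed equal correlations between waves. Loss or shrinkage of the 6-month effect is possible under two of the models allowed, but it is not established.

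The consequence is confined to secondary outcomes. The WLQ is outside the point because it has no baseline score. The Cox analysis of time to sustainable return to work and the sample size of 172 are not affected.

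**What to change.** For the 4DSQ, SF-36, Euroqol and ASE, state in advance that:

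- the baseline score of the outcome is a covariate regardless of observed imbalance (or, equivalently in aim, baseline is kept as an outcome with its means constrained equal between arms);
- the 6- and 12-month scores are modelled with wave as a category, arm and arm-by-wave, keeping random effects for participant and team;
- the arm difference is reported at 6 months, at 12 months and averaged over both.

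If the full analysis plan already says this, a confirming sentence is enough. The cost is a sentence or two of analysis wording, since every score needed is already scheduled in Table 1.

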#### Economic evaluation

Cost-effectiveness will be assessed from both the social insurer’s perspective and the societal perspective by dividing the incremental costs by the incremental effects. The incremental cost-effectiveness ratio (ICER) represents the additional costs needed to gain one extra unit of effect in the intervention group compared to the control group. Cost-utility will be measured by dividing the differences in total costs by the difference in QALYs between the two groups.

A cost-benefit analysis will be conducted from the societal perspective. The net monetary benefit will be calculated by subtracting the difference in total costs between the two groups from the differences in productivity gain. Return on investment will be measured by dividing the incremental benefit (gain minus costs) by the incremental costs of the investment.

Bootstrapping will be used to estimate uncertainty surrounding the incremental costs. Confidence intervals (95%) around the mean costs differences will be computed by bias corrected and accelerated bootstrapping.

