 For workers without a permanent employment contract, it is possible that the sickness benefit ends, before full RTW is achieved. The worker can be recovered from illness or functional limitations (assessed with regard to last or previous work) without actual RTW, because the worker has no workplace to return to. Therefore, in line with Vermeulen and colleagues, the duration of the sickness benefit period will be assessed as well. This is defined as the duration of the sickness benefit from the day of enrolment until ending of the sickness benefit for at least 28 consecutive calendar days [21]. Additionally, the total number of days of sickness benefit during follow-up will be calculated. Awarded sickness benefit claims during follow-up are only included in the calculation when the participant is sick-listed due to the same (or related) mental disorder [21]. Data on sickness benefit will be collected from the SSA database and by self-report of the participants.

– *Work status*

 Work status is defined as the average number of hours worked per week during the one-year follow-up. In addition to a self-administered questionnaire, the SSA database will be used to collect this information.

– *Severity of mental disorder symptoms*

 Severity of mental disorder symptoms will be assessed using the Four-Dimensional Symptom Questionnaire (4DSQ) [34].

– *Perceived general health status*

 Using the Dutch translation of the SF-36 [35] perceived general health status will be measured.

– *Quality of life*

 Quality of life will be measured using the Dutch translation of the Euroquol questionnaire [36].

– *Attitude, Social influence, and self-Efficacy (ASE)*

 For the development of earlier participatory RTW programs the Attitude-Social influence-self-Efficacy (ASE) model was used as an underlying theoretical framework [37,38]. In these studies the ASE constructs were assessed using a questionnaire developed by Van Oostrom and colleagues [39]. In this study we will make use of the same questionnaire.

– *Work limitations*

 Work limitations will be measured with the Dutch translation of the Work Limitations Questionnaire (WLQ) [40].

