### Randomisation procedure

Randomisation will take place on participant level. In line with previous research by Vermeulen et al. [21] pre-stratification of participants is based on information about type of worker before reporting sick, i.e. unemployed worker, temporary agency worker or fixed-term contract worker. To ensure an equal distribution of control group participants and intervention group participants in the three different SSA districts, participants will also be pre-stratified on district-level. Schemes with random permuted numbers will be used by the principal investigator to generate separate block randomisation tables with fixed block sizes of four.

Randomisation takes place during the intake appointment at the SSA office. After the informed consent form is signed and the baseline questionnaire is completed by the participant, the assistant of the SSA contacts the research assistant at the VU Medical Centre to perform the randomisation. The research assistant of the VU Medical Centre uses the block randomisation table of the correct stratum to determine the randomisation result. The participant will be informed immediately about the randomisation result, intervention or control group, and the consecutive steps. Participants who are allocated to the intervention group will be assigned to an intervention team of the corresponding SSA office for guidance according to the participatory supportive RTW program in combination with usual OHC. These intervention teams will not be involved in the guidance of control group participants. Control group participants will be assigned to a team of the corresponding SSA office that is not familiar with the intervention program.

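### The cost-utility analysis fixes no baseline-utility adjustment for the QALY difference and leaves it to a data-driven rule that does not clearly cover Euroqol

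*Protocol article*

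**What the plan says.** All references are to the protocol article.

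- **Cost-utility** (Statistical analysis, Economic evaluation): "Cost-utility will be measured by dividing the differences in total costs by the difference in QALYs between the two groups". No covariate is named, and the sentence does not say whether either difference is adjusted.
- **Utility measure** (Outcomes, Effect evaluation, among the secondary outcomes): "Quality of life will be measured using the Dutch translation of the Euroquol questionnaire". The row of Table 1 that begins "Quality of life (Euroqol" is marked at baseline, 6 and 12 months. The Tic-P row is marked at baseline and at every follow-up.
- **Adjustment rule** (Statistical analysis, opening paragraph): "Descriptive statistics will be used to check for dissimilarities of prognostic factors in the two groups at baseline". The next sentence is "If necessary, analysis will be adjusted". By its position this covers both the effect and the economic evaluation.
- **Other secondary outcomes** (Statistical analysis, Effect evaluation): "Differences in other secondary outcome measures will be analysed with the use of longitudinal random coefficient analysis". This is not linked to the QALY.
- **Stratification** (Randomisation procedure): type of worker, and in addition "participants will also be pre-stratified on district-level". Baseline utility is not a stratification factor.
- **Uncertainty** (Statistical analysis, Economic evaluation): "Bootstrapping will be used to estimate uncertainty surrounding the incremental costs". Incremental QALYs are not mentioned there.

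**The concern.** When utility is measured at the start of follow-up, the baseline value is normally part of the QALY, and later values correlate with it. A chance difference in baseline utility between the arms therefore shows up in part as a QALY difference that treatment did not cause. Stratifying on worker type and district does not prevent this.

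The usual remedy is to put baseline utility in the model in every case. The article instead adjusts only if a descriptive comparison suggests a need. It gives no threshold, so the decision follows sight of the data. It also speaks of prognostic factors, and neither the Prognostic measures section nor the prognostic block of Table 1 lists Euroqol utility or Tic-P costs. Even when baseline utility looks balanced, leaving it out gives up precision. At stake is how precise and how pre-specified the cost-utility denominator is, in a trial whose stated aim is cost-effectiveness.

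**Working it through.** **Plan's own figures.** The article gives no QALY, utility or cost-utility figure, so there is none to reproduce. The only stated figure used below is the sample size, and it does reproduce:

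- A hazard ratio of 2.0 with 80% power and two-sided 5% needs 66 events (Schoenfeld). 66/(2/3) = 99, against 100 stated.
- Sixteen teams and an ICC of 0.05: N = 100 × [1 + (N/16 − 1) × 0.05] gives N = 138.2. Dividing by 0.8 gives 172.7, against 172 stated (86 per arm).
- After 20% loss: 86 × 0.8 = 68.8, about 69 per arm.

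**Assumptions, not in the article.** Trapezium-rule QALY over one year; utility SD 0.20 to 0.30, equal at each visit; the same correlation ρ between any two visits, 0.3 to 0.7; clustering within teams ignored.

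**Step 1, weights.** With visits at 0, 6 and 12 months, QALY = 0.25·U0 + 0.50·U6 + 0.25·U12.

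**Step 2, share of a baseline difference carried into the QALY difference.** Share = 0.25 + 0.75ρ, that is 0.475, 0.625 and 0.775 for ρ = 0.3, 0.5 and 0.7. The carry-over is partial.

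**Step 3, how large a chance imbalance could be.** The 95% limit of the baseline difference is 1.96 × SD × √(2/n).

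| | 86 per arm | 69 per arm |
|---|---|---|
| Baseline utility difference, SD 0.20 to 0.30 | 0.060 to 0.090 | 0.067 to 0.100 |
| Through the baseline weight alone (× 0.25) | 0.015 to 0.022 | 0.017 to 0.025 |
| Including correlation (× 0.475 to 0.775) | 0.028 to 0.069 | 0.032 to 0.078 |

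The last two rows are in QALYs.

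**Step 4, precision.** In units of SD², the QALY variance is 0.375 + 0.625ρ unadjusted. After adjustment for U0 it is that value minus (0.25 + 0.75ρ)². The standard error (SE) of the group difference is SD × √(2 × variance/n). With SD 0.25:

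| ρ | Variance, unadjusted | Variance, adjusted | SE, 86 per arm | SE, 69 per arm | SE reduction |
|---|---|---|---|---|---|
| 0.3 | 0.5625 | 0.337 | 0.029 to 0.022 | 0.032 to 0.025 | 23% |
| 0.5 | 0.6875 | 0.297 | 0.032 to 0.021 | 0.035 to 0.023 | 34% |
| 0.7 | 0.8125 | 0.212 | 0.034 to 0.018 | 0.038 to 0.020 | 49% |

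The percentage reduction does not depend on the SD or on n.

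**Step 5, sensitivity to the correlation pattern.** Take ρ = 0.5 with baseline but 0.6 between the two follow-ups. The variance is then 0.7125 unadjusted and 0.7125 − 0.625² = 0.322 adjusted, which is 55% less. With SD 0.25 and 68.8 per arm the SE falls from 0.036 to 0.024. The picture is the same.

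No comparable figure is offered for costs, because the article gives nothing from which to size it.

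**The case against.** The strongest case against has three parts.

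**The text does not specify an unadjusted estimator.** A reader might infer that the plan commits to the raw difference in QALYs. It does not say so. The sentence defines a ratio, and a regression-adjusted difference would satisfy it. The general adjustment rule also stands above the economic evaluation and addresses chance imbalance. This part stands, and it limits the point to what is not fixed in advance. The rule is still no cure: it depends on the data, names no covariate, and is tied to prognostic factors, among which utility is not listed.

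**QALY formula and covariates usually belong in the analysis plan.** That is so, and their absence from an article is not the complaint. The complaint is that the article does state a rule for when to adjust, and that rule suits the QALY poorly. Baseline utility belongs in the model because it is a component of the outcome, not because it happens to look unbalanced.

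**The effect is easily overstated.** A reader might infer that imbalance passes in full into the ratio, that the ratio is biased, or that a small denominator could change sign. The documents support none of these. The carry-over is partial. Under randomisation the unadjusted difference is unbiased: in the Step 5 case a one-SE baseline imbalance (0.043) shifts the QALY difference by 0.625 × 0.043 = 0.027, which is a component of the ordinary SE of 0.036 and not an addition to it. The article gives no expected QALY difference, so nothing can be said about how small the denominator is.

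**Conclusion.** The point holds in a limited form. The article fixes no baseline adjustment for the QALY or cost difference and relies on a conditional rule that does not clearly cover Euroqol utility. The consequence is conditional imbalance and lost precision, plus an analysis decision left until the data have been seen. It is not systematic bias.

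On size, about 0.48 to 0.78 of any chance baseline utility difference would enter the QALY difference, and adjustment would cut its SE by about 23% to 49%. Both ranges rest on a trapezium QALY and correlations of 0.3 to 0.7, none of which the article states. The absolute SEs also rest on an assumed SD. The direction holds for any positive correlation; the exact gain is uncertain. The primary return-to-work analysis is unaffected.

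**What to change.** In Statistical analysis, Economic evaluation, state that:

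1. The QALY difference will be estimated by regression on arm, with baseline Euroqol utility and the stratification factors (worker type and district) as covariates, regardless of observed imbalance.
2. The cost difference will be estimated by regression on arm with baseline Tic-P costs as a covariate.
3. Both adjusted differences will be bootstrapped jointly, by resampling participants and refitting both models each time, and these differences will form the cost-utility ratio.

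The cost is analysis wording only. Baseline Euroqol and Tic-P are already scheduled, and no figure stated in the article changes. If a separate analysis plan already specifies this, it is enough to bring the two texts into line.

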### Economic evaluation

Direct and indirect costs will be measured to conduct an economic analysis from the social insurer’s perspective and the societal perspective.

Costs for health care utilization, OHC and investments in vocational rehabilitation support made by the SSA are considered as direct costs. Examples of investments made by the SSA are training or education, interventions aimed at health promotion and contracting a rehabilitation agency to search for a workplace.

Indirect costs are related to paid sickness benefits. In case an employee becomes sick-listed, loss of productivity is normally considered to be part of the indirect costs. However, because sick-listed temporary agency workers, unemployed workers and workers with an expired fixed-term employment contract no longer have an employment contract, loss of productivity does not result in indirect costs [23]. Unemployed workers and workers whose employment contract ended during sickness absence have no workplace (anymore), which means there is no loss of productivity. The sick-listed temporary agency worker will, in case of sick-listing, be replaced with a healthy worker, which results in no productivity loss for the company concerned.

Data on paid sickness benefits and costs for investments made by the SSA will be collected from the SSA database and the worker’s files after one year follow-up. Data on OHC by the SSA professionals, i.e. number of consults during follow-up and type of OHC professional, will be collected from the SSA database and the medical files. Health care utilization will be measured by the Trimbos/iMTA questionnaire for Costs associated with Psychiatric Illness (Tic-P) [43]. The Tic-P is developed to measure health care utilization of people with mental illnesses. It quantifies the number of visits to different health care providers. Prices for different health care services suggested in guidelines for economic evaluation in the Netherlands will be used to value the health care consumption [44].

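### As written, the societal net monetary benefit credits saved sickness benefit on top of productivity gain, so it is overstated by the benefit saved if benefit payments fall

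*Protocol article*

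**What the plan says.** Two sections, both headed Economic evaluation, have to be read together.

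- **Under Methods/Design (cost definitions).** One set of costs serves two perspectives: "Direct and indirect costs will be measured to conduct an economic analysis from the social insurer’s perspective and the societal perspective". Direct costs: "Costs for health care utilization, OHC and investments in vocational rehabilitation support made by the SSA are considered as direct costs". Indirect costs: "Indirect costs are related to paid sickness benefits". Productivity is kept out of the indirect costs: for these workers "loss of productivity does not result in indirect costs". Two reasons follow. Unemployed workers and those whose contract has ended "have no workplace (anymore), which means there is no loss of productivity". A sick agency worker is replaced by a healthy one, "which results in no productivity loss for the company concerned".
- **Under Statistical analysis (formulas).** The cost-benefit analysis takes society's viewpoint: "The net monetary benefit will be calculated by subtracting the difference in total costs between the two groups from the differences in productivity gain". Gain minus costs, divided by the incremental cost of the investment, gives the return on investment. The cost-effectiveness ratio (both perspectives) and the cost-utility ratio use incremental or total costs, with no productivity term.

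Neither section removes sickness benefits from the societal total.

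**The concern.** A sickness benefit moves money from the public insurer to the worker. It is a real cost to the insurer. To society it is a transfer and uses no resource. If a participant returns to work earlier and the benefit stops, the formula books both the production gained and the benefit no longer paid.

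Reading the benefit as a stand-in for lost production does not help, because production would then enter twice, once as saved benefit and once as productivity gain.

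Cost-effectiveness is the trial's stated objective, and the Discussion says the results will show whether the programme outweighs its societal costs. An error in the societal net benefit bears directly on that statement.

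**Working it through.** The article states no net benefit, wage, benefit level or programme cost, so there is no figure to reproduce. The check is algebraic, followed by an illustration.

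**Notation** (differences, intervention minus control): dP = productivity gain; dD = direct costs; dB = paid sickness benefits.

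**Step 1, total costs** (Methods/Design): dC = dD + dB.

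**Step 2, net benefit as written** (Statistical analysis): NMB = dP − dC = dP − dD − dB.

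**Step 3, net benefit without the transfer:** dP − dD.

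**Step 4, difference:** (dP − dD − dB) − (dP − dD) = −dB.

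- Benefit falls (dB < 0): NMB is too high by the benefit saved.
- Benefit unchanged: no excess.
- Benefit rises: NMB is too low by the increase.

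The same amount enters the numerator of the return on investment.

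**Step 5, sign.** With benefit saved S = −dB > 0, the plan reports a positive figure where the transfer-free figure is negative whenever dP < dD < dP + S.

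**Illustration of scale.** The Sample size section assumes a hazard ratio of 2.0 and return to work in 2/3 of participants by 12 months. With constant hazards, equal arms and 2/3 read as the pooled proportion, let x be the control-arm proportion not yet returned at 12 months:

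- (x + x²)/2 = 1/3, so x = 0.4574
- control hazard = −ln x = 0.7821 per year
- restricted mean, control: 365 × (1 − 0.4574)/0.7821 = 253.2 days
- restricted mean, intervention: 365 × (1 − 0.2092)/1.5643 = 184.5 days
- difference: 68.7 days

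The daily benefit (EUR 30 to 70) and the share of these days that are also saved benefit days are assumptions, not figures from the documents. Excess per participant = 68.7 × share × daily benefit:

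| Share of days that save benefit | EUR 30 | EUR 50 | EUR 70 |
|---|---|---|---|
| 100% (full overlap) | 2,061 | 3,435 | 4,809 |
| 50% | 1,031 | 1,718 | 2,405 |
| 0% | 0 | 0 | 0 |
| −25% (benefit days rise) | −515 | −859 | −1,202 |

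**Worked sign change.** In units of one day's last wage, assume new earnings equal to the last wage, benefit at 70% of it and full overlap. Then dP = 68.7 and S = 0.7 × 68.7 = 48.1. The sign is wrong for any dD between 68.7 and 68.7 + 48.1 = 116.8 daily wages. At an assumed dD of 90, the plan gives 68.7 − 90 + 48.1 = 26.8, and the transfer-free figure is 68.7 − 90 = −21.3. With a cheaper programme the sign holds: at dD = 40 the two figures are 76.8 and 28.7.

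**The case against.** **This is a condensed article.** Assigning cost items to perspectives could be left to a full economic plan, and the Discussion names societal costs and the agency's expenditure separately. That lowers the certainty about what will finally be computed. It does not remove the point, because the article states both the cost list and the formula, and following them as stated gives the wrong societal figure.

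**A reader might infer a flat contradiction on productivity.** The text does not support that. The cost section denies a productivity loss from sick-listing; it does not deny every productivity effect. A worker without a workplace can lose no output by falling ill and still add output once placed in a job. A tension remains. If a replaced worker's absence costs nothing, the same logic raises the question of how much output is added by filling a job that someone else could have filled. The article does not address this.

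**A reader might extend the double counting to the cost-effectiveness and cost-utility ratios.** Neither contains a productivity term, so nothing is counted twice there. In a societal version of either ratio the issue is only that a transfer is counted as a societal cost. The direction of a correction depends on the treatment of production. Removing benefits alone makes a programme that saves benefit look worse. Replacing them with production at a full wage per day makes it look equal or better whenever the benefit is at most the wage.

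**A reader might take the overstatement as certain.** It is conditional. The Outcomes section notes that benefit can stop before return to work, and the section on placement allows up to three months of placement with benefit continuing. Saved benefit days and earlier working days therefore overlap only in part.

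**A reader might size the effect from the earlier trial's medians** (299 − 161 = 138 days). The Background section rules this out: in that trial benefit was paid during therapeutic placement, and the programme cost the insurer more than usual care. Those are also medians in workers with musculoskeletal disorders, not mean benefit days saved.

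**Conclusion.** The point holds for the societal cost-benefit analysis and the numerator of the return on investment. As written, both differ from the transfer-free figure by exactly −dB. They are overstated by the benefit saved if the programme reduces benefit paid, which is its stated intention; unaffected if benefit does not change; and understated if it rises. The sign is wrong only when the added direct cost lies between the productivity gain and that gain plus the benefit saved.

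The result rests on reading total costs in the formula as the direct and indirect costs defined earlier in the article, the only definition given. The actual size cannot be obtained from the documents. The range of about EUR 2,100 to 4,800 per participant is an illustration under the design hazard ratio, assumed daily benefits and full overlap of days, and it shrinks to zero or reverses as overlap falls.

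In the societal cost-effectiveness ratio and any societal cost-utility ratio, the defect is a transfer booked as a societal cost, without double counting. The insurer's analysis, where benefit is a genuine cost, and the primary hazard ratio are untouched.

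**What to change.** 1. Define total costs separately for each perspective.
2. Exclude sickness benefits from total costs in the societal cost-benefit analysis and return on investment. Exclude them from other societal totals too, or show them there as a separate transfer line. Keep them as a cost in the insurer's analysis.
3. Count production once, from hours worked, and state how it is valued.
4. State how the productivity gain fits with the position that sick-listing causes no productivity loss, including whether the replacement argument also applies to the jobs participants take up.

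This is a change of wording. Benefit payments and hours worked are already to be collected from the agency's database, and hours also from the questionnaires. The price is that the societal cost-benefit result will look less favourable if benefit payments fall.
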